## Abstract

**Background:**

Effective clinician-patient communication about health behavior change is one of the most important and most overlooked strategies to promote health and prevent disease. Existing guidelines for specific health behavior counseling have been created and promulgated, but not successfully adopted in primary care practice. Building on work focused on creating effective clinician strategies for prompting health behavior change in the primary care setting, we developed an intervention intended to enhance clinician communication skills to create and act on teachable moments for smoking cessation. In this manuscript, we describe the development and implementation of the Teachable Moment Communication Process (TMCP) intervention and the baseline characteristics of a group randomized trial designed to evaluate its effectiveness.

**Methods/Design:**

This group randomized trial includes thirty-one community-based primary care clinicians practicing in Northeast Ohio and 840 of their adult patients. Clinicians were randomly assigned to receive either the Teachable Moments Communication Process (TMCP) intervention for smoking cessation, or the delayed intervention. The TMCP intervention consisted of two, 3-hour educational training sessions including didactic presentation, skill demonstration through video examples, skills practices with standardized patients, and feedback from peers and the trainers. For each clinician enrolled, 12 patients were recruited for two time points. Pre- and post-intervention data from the clinicians, patients and audio-recorded clinician‒patient interactions were collected. At baseline, the two groups of clinicians and their patients were similar with regard to all demographic and practice characteristics examined. Both physician and patient recruitment goals were met, and retention was 96% and 94% respectively.

**Discussion:**

Findings support the feasibility of training clinicians to use the Teachable Moments Communication Process. The next steps are to assess how well clinicians employ these skills within their practices and to assess the effect on patient outcomes.

**Trial Registration:**

ClinicalTrials.gov Identifier: NCT01575886

## Background

Effective clinician-patient communication about health behavior change is one of the most important and overlooked strategies to promote health and prevent disease
[1-3]. Modifiable behavioral risks such as tobacco use, lack of exercise, and poor diet choices contribute to more than 50% of preventable mortality and morbidity in the United States
[4-7].Nationally, 87% of adults visiting a primary care clinician are overweight, smoke cigarettes or fail to exercise at the recommended levels
[8]. Most Americans see a primary care clinician at least once during the year
[9], providing a unique opportunity to reach the majority of the population with health behavior change messages that are tailored by knowledge of medical history and a continuity relationship. While guidelines for specific health behavior counseling have been created and promulgated
[10-13],evidence of the successful adoption of such research findings in actual primary care settings is often lacking
[14,15].Potential barriers to implementation include concerns about competing demands for time
[16-19], anticipated patient resistance to cessation counseling
[20-22],and the lack of effective strategies for accomplishing the recommendations within the routine flow of patient care.

Our ongoing research is generating rich evidence about clinicians’ natural use of ‘teachable moments’ for addressing health behavior change during the primary care outpatient visit
[23,24]. A teachable moment involves linking a health behavior to a salient patient problem and creating an opportunity for effective health behavior change discussions
[25]. While clinicians commonly use teachable moments to *initiate* health behavior talk, communication skills for navigating patient resistance to behavior change are generally lacking, resulting in inefficient and ineffective use of time. This deficiency in communication skills may be overcome by pragmatically adapting aspects of behavioral counseling to the primary care setting. For example, brief motivational interviewing and patient-centered therapy techniques promote specific communication skills for eliciting the patient’s perspective, adapting to resistance, and partnering to encourage behavior change
[26-28].These strategic communication skills complement the teachable moment, and create a context conducive to health behavior change.

Building on this work and partnering with experts in medical education and communication, we developed a communication process that teaches clinicians to capitalize on teachable moments by providing them with specific communication techniques that can be realistically translated into busy primary care practices with potentially powerful effects. We designed a group randomized trial to evaluate the effectiveness of this clinician-focused intervention. In this manuscript, we describe the overall research design, the development and design of the Teachable Moment Communication Process (TMCP) intervention, and the baseline characteristics of the participating clinicians and patients. We also report participant feedback regarding the clarity and utility of the intervention.

## Methods/Design

### Study aim

The overall aim of the clinical trial is to implement and evaluate a clinician‒focused intervention designed to facilitate health behavior change discussion. The two study questions are: 1) Does the TMCP intervention increase clinician use of the teachable moment communication process in the clinician's own practice?, and 2) Does use of the TMCP improve immediate and intermediate patient report outcomes related to smoking?

### Study design

The study design is a group randomized trial of 31 clinicians. Clinicians were randomized to either the intervention group or a delayed intervention group. Clinicians randomized to the delayed intervention group receive an attention control consisting of a multimedia education resource for colon cancer screening. After evaluation at the post-intervention data collection period, the delayed intervention group will cross over and receive a revised TMCP intervention (see Figure 
1). The University Hospitals, MetroHealth Medical Center, and Cleveland Clinic Institutional Review Boards approved the study procedures.

**Figure 1 F1:**
[figure not shown]
Study design and physician and patient samples.

### Clinician recruitment

The Research Association of Practices (RAP), a practice-based research network, and community satellite practices affiliated with one of the three main health care systems in the area, were the starting points for recruiting clinician participants. Clinicians were required to be in a community practice (i.e. not a residency practice or a practice located within the hospital), have a minimum of 2 patient care days per week, see predominately adult patients, and be located within 25 miles of the research center. The study was introduced with email invitations and in-person group presentations about the project. All clinicians were asked to complete a screening form, which included demographics, practice characteristics, contact information and level of interest in the study. One on one meetings were conducted with interested clinicians to provide further details about participation, address questions, and, if interested, complete the informed consent process. Consented clinicians were asked if they had any colleagues who might be interested in participating, and any referred clinicians were contacted directly by phone or email about the study. Two additional exclusion criteria were added after the recruitment process began: a) clinicians who reported plans to leave practice in the next year, and b) reported average patient waiting times of less than five minutes. Figure 
2 shows recruitment frequencies for clinicians approached for participation in the study.

**Figure 2 F2:**
[figure not shown]
Physician recruitment for study participation.

The project coordinator worked with the clinician and his/her staff to schedule all data collection sessions and intervention training session dates. Clinician participants were told the study was about communication and health behavior change, but were blinded to the specific health behavior advice hypotheses. After beginning data collection, low accrual of patients for some clinicians made it infeasible to complete data collection within the study time frame. If the study team was not able to successfully recruit one patient after 20 hours of data collection effort at a clinician's practice, that clinician was ineligible for continued participation in the study. Four clinicians were excluded because of low volume of eligible patients.

### Randomization

The unit of randomization for this study was the clinician. Clinicians were randomized to the intervention and delayed intervention groups using covariate adaptive randomization
[29]. Covariate adaptive randomization increases power and validity through selected covariate and sample size balance. New participants were assigned to the intervention group based on two specific covariates; sex and practice system, as well as previous assignments of participants already randomized. In the event that clinicians were from the same practice and practiced closely together (e.g. shared patient panels, husband and wife practicing together) they were randomized together. This decision was to reduce the chance of cross contamination through exposure to the intervention content by clinicians in the same practice but randomized into different intervention arms. Clinicians were enrolled on a continuous basis over the start-up period. Those clinicians determined to be ineligible after randomization were replaced by the next clinician enrolled in the study with the same covariate profile. This occurred for two cases.

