### Data management & analysis

Survey data were entered into a Research Electronic Data Capture (REDCap) database hosted by Case Western Reserve University. REDCap is a secure, web-based application designed to support data entry, manipulation, reporting and export to statistical packages for research studies. Audio recordings were uploaded to a secure server to be coded qualitatively for elements of the TMCP. Upon completion of data collection, coding and survey data will be merged and analyzed using SAS statistical software v9.2 (Cary, NC). Survey and audio data were routinely monitored for completeness and quality over the course of data collection.

Data analyses reported in this manuscript include descriptive statistics of enrolled clinicians and patients in Cohorts 1 and 2. Demographic characteristics, visit characteristics and baseline smoking behavior were examined across all patients enrolled in the study. Characteristics of patients who declined participation were compared to those who enrolled in the study using Chi-square tests for categorical variables. Because the continuous variable number of cigarettes per day was not distributed normally, a Wilcoxen Rank Sum test was used to evaluate median differences between groups.

In future analyses of the overall study aims, the main independent variable will be the exposure to the TMCP intervention at the clinician level. All outcome variables are evaluated at the patient level and will be adjusted for the clustering of patients within clinicians using generalized linear mixed models (GLMM). First, we will examine clinician and patient characteristic differences at baseline (Cohort 1) between the TMCP intervention group (I) and the delayed intervention group (DI) using chi-square and t-tests. Differences with an effect size of 0.3 of a standard deviation for continuous variables, or 20% for categorical variables will be considered clinically significant and will be included in subsequent analyses as potential confounding variables.

The coded variables from the audio recording of the patient visits will be examined for Cohort 1. For this comparison, we expect that the I and DI groups will be similar in the use of the TMCP skills. The general model for these comparisons:

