(1)$${\text{y}}_{\text{ij}}={\text{p}}_{0\text{j}}+{\text{p}}_{1\text{j}}{\left(\text{Patient characteristic A}\right)}_{\text{ij}}+{\text{p}}_{2\text{j}}{\left(\text{Visit characteristic b}\right)}_{\text{ij}}+{\text{e}}_{\text{ij}}$$

(2)$${\text{p}}_{0\text{j}}={\text{b}}_{00}+{\text{b}}_{01}\left(\text{TMCP Group}:\text{I}=1,\text{ DI}=0\right)+{\text{b}}_{02}\left(\text{Clinician characteristic C}\right)+{\text{r}}_{0\text{j}}$$

The Level 1, or patient visit level model represents the outcome (i.e. teachable moment communication process occurred) as a function of the clinicians mean at baseline plus a random error. Baseline patient or visit level confounding variables will be included in the model as covariates. The clinician level (Level 2) models specify the relationship between the clinician-level predictors and the coefficients in the Level 1 model, with a random effect. Additional clinician level covariates may be included at this level. β_00_ represents the mean outcome score across clinicians, TMCP group indicates the intervention condition and β_01_ represents difference in the outcome score that is attributed to the group assignment, controlling for other clinician and patient level variables in the model.

In this study design, the outcome measures are derived from the audio recordings and patient survey of a sample of patients at each time point. These data do not reflect repeated measures on the same patients across the time points, but rather separate cross-sectional cohorts. Thus, the model for the examination of Aim 1 will include a dummy variable at the patient level to indicate the cohort (Cohort 1 versus Cohort 2). We hypothesize that the odds of performing key elements of the TMCP during smoking cessation talk with patients will be twice as high for the intervention group as the delayed intervention group. For Aim 2, the attention will turn to the outcomes of patient recall and reported usefulness of smoking discussion, intention to quit, IBC-T change scores, and smoking status. Satisfaction with the communication and the duration of the visit in minutes will also be evaluated as potential adverse effects. The same generalized linear mixed model will be used with the indicator of TMCP group as the key independent variable.

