## Results

Characteristics of participating clinicians randomized to intervention groups are displayed in Table 
2. As evidence of satisfactory randomization, intervention and delayed intervention clinicians were similar in regard to all examined demographic information and practice characteristics.

**Table 2 T2:** Characteristics of participating clinicians randomized to initial intervention and delayed intervention groups

	**Total** **(n = 31)**	**Delayed Intervention** **(n = 15)**	**Intervention** **(n = 16)**	***P***
Female (%)	48	47	50	0.85
Race, white (%)	87	87	88	0.95
Training (%)				
Internal Medicine	23	20	25	0.32
Family Medicine	71	80	63	
Nurse Practitioner	6	0	13	
Safety net practice (%)	65	67	63	0.81
Years since residency completed, mean	17.4	18.7	15.3	0.37
Patient care days per week, mean	4.1	4.0	4.1	0.75
Speaks Spanish during visits (%)	19	20	19	0.93

Sixty-nine percent of eligible patients agreed to participate in the study; their characteristics and the characteristics of eligible patients who declined participation are shown in Table 
3. Patients who enrolled in the study were more likely to be female and African-American than those who declined. To further support randomization, patient participants seeing clinicians in the intervention and delayed intervention groups were not significantly different on the basis of any patient characteristics.

**Table 3 T3:** Characteristics of patients that declined participation and enrolled in study

	**Declined** **(n = 371)**	**Enrolled** **(n = 840)**	***P***
Age category (%)			
18 to 29 years	18	16	0.37
30 to 39 years	19	18	
40 to 49 years	24	24	
50 to 59 years	24	29	
60 to 70 years	15	12	
Female (%)	54	61	0.01
Hispanic (%)	12	10	0.17
Race (%)			
White	64	56	<0.001
Black, African-American	23	34	
Other / more than one	12	7	
Education (%)			
Less than high school graduate	21	22	0.84
High school graduate or GED	37	35	
Some college	30	31	
College graduate	12	13	
Self-reported health status (%)			
Excellent	6	6	0.83
Very good	15	15	
Good	32	33	
Fair	31	30	
Poor	15	17	
Chronic conditions (%)			
None	51	49	0.12
One	28	25	
Two or more	20	26	
Seeing regular doctor (%)			
First visit	28	23	0.26
Known less than 1 year	14	19	
Known more than 1 year	58	59	
Reason for visit (%)			
New illness or problem	31	27	0.38
Continued care	44	48	
Well care, physical	25	25	
No. cigarettes smoked / day, median (IQR)	10 (5–20)	10 (5–20)	0.99
Considering quitting within the (%)			
Next month	----	28	

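### The two factors used to balance the allocation, clinician sex and practice system, are not prespecified in the outcome models, and the only stated criterion for covariate entry will usually pass over them

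*Protocol article*

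**What the plan says.** The Randomization section of the protocol article states: "Clinicians were randomized to the intervention and delayed intervention groups using covariate adaptive randomization". It names the balancing factors: "New participants were assigned to the intervention group based on two specific covariates; sex and practice system". It also gives the reason for the method: "Covariate adaptive randomization increases power and validity through selected covariate and sample size balance".

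The Data management & analysis section sets the covariate rule. Arms are compared at baseline (Cohort 1), and "Differences with an effect size of 0.3 of a standard deviation for continuous variables, or 20% for categorical variables will be considered clinically significant"; such variables "will be included in subsequent analyses as potential confounding variables". The model is a generalized linear mixed model with a random clinician effect. Its Level 2 equation holds the group indicator and one generic clinician characteristic. For other clinician variables the text says only: "Additional clinician level covariates may be included at this level". Neither sex nor practice system is named in any model.

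The Results section reports that "intervention and delayed intervention clinicians were similar in regard to all examined demographic information and practice characteristics". Table 2 gives 50% female in the intervention arm (n = 16) and 47% in the delayed arm (n = 15).

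**The concern.** The allocation and the covariate rule pull in opposite directions. The allocation makes the arms alike on sex and practice system. The rule brings variables in because the arms differ on them. It will therefore tend to miss the two variables that the design singled out as worth balancing.

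Balancing makes the estimated group difference more precise if the factors predict outcome. A model without the factors cannot see this: it leaves the variation they explain in the clinician random effect and reports a standard error as if allocation had been simple. The true precision is better than the reported one, and the gain the article claims for the method does not reach the test. With 31 clinicians, between-clinician precision is the scarce resource.

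**Working it through.** **Would the rule select the balancing factors?** From Table 2, 8/16 − 7/15 = 3.3 percentage points for female sex. This is far below 20%, whether read as points or as a relative difference (3.3/46.7 = 7%). Practice system is not tabulated (safety net practice is a different variable), so its observed balance cannot be checked.

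A simulation of minimization shows what to expect (31 clinicians, biased coin 0.8, sex and three equal systems assumed, 3,000 runs per setting). A sex gap of 20 points or more arises in about 1% of trials. A gap that large in any one system arises in about 5–6%.

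By contrast, years since residency (18.7 vs 15.3, P = 0.37) may enter. If that P is from a two-sided t-test on 15 and 16 clinicians, |t| ≈ 0.91 and the standardized difference is 0.91 × √(1/15 + 1/16) ≈ 0.33, above 0.3. The numbers with data are not stated, so this is only an illustration.

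**How much precision is at stake?** From the article: 31 clinicians and m = 13.8 patients per clinician. That figure must be per cohort, since 840/31 ≈ 27 over both cohorts. Assumed: the ICC (ρ) and the share R² of between-clinician variance explained by the two factors. For a linear outcome and perfect balance:

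- Variance ratio, adjusted to unadjusted: V = 1 − R²ρ / (ρ + (1 − ρ)/m)
- SE inflation without adjustment: 1/√V
- True size of the nominal 5% test: 2 × (1 − Φ(1.96/√V))
- Power after adjustment where the unadjusted SE implies 80%: Φ(2.80/√V − 1.96)

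Worked case, ρ = 0.05, R² = 0.2: (1 − 0.05)/13.8 = 0.0688, so V = 1 − 0.010/0.1188 = 0.92.

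| ρ | R² | V | SE inflation | True size | Power |
|---|---|---|---|---|---|
| any | 0 | 1.00 | 0% | 5.0% | 80% |
| 0.02 | 0.1 | 0.98 | 1% | 4.8% | 81% |
| 0.20 | 0.1 | 0.92 | 4% | 4.1% | 83% |
| 0.05 | 0.2 | 0.92 | 4% | 4.1% | 83% |
| 0.10 | 0.4 | 0.76 | 15% | 2.4% | 90% |
| 0.20 | 0.5 | 0.61 | 28% | 1.2% | 95% |

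**Check by simulation.** The same minimization scheme was analysed with linear models on clinician means, with and without sex and system.

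- SE against true sampling SD, no adjustment: 0.145 vs 0.147 at ρ = 0.10, R² = 0 (no inflation); 0.146 vs 0.127 at ρ = 0.10, R² = 0.5 (15% too large; the formula gives 20% because it assumes perfect balance).
- Type I error over ρ = 0.02–0.20: without adjustment, 0.028–0.042 at R² = 0.3 and 0.022–0.045 at R² = 0.5; with adjustment, 0.045–0.054 over all R² examined (0 to 0.5).
- Power for a 0.3 SD effect at ρ = 0.05: adjustment takes it from 0.645 to 0.695 at R² = 0.3 and from 0.651 to 0.734 at R² = 0.5. At R² = 0 it falls from 0.642 to 0.628.

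The article's planned minimum of 28 physicians with 12 patients per cohort cannot be reproduced, because alpha, power and ICC are not stated.

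**The case against.** A reader might infer that covariates can enter only if imbalanced, so that sex and practice system are shut out and the standard errors are certain to be too large. The text does not say this. It makes imbalance a sufficient reason for entry, not a necessary one. The Level 2 equation has an open slot for a clinician characteristic, further clinician covariates are allowed, and nothing excludes the balancing factors. This objection stands: the accurate statement is that they are not prespecified.

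It can also be said that a journal article leaves the final covariate list to an analysis plan. That would answer a mere omission. Here, however, the article states a criterion with thresholds, and that criterion works against the design it describes. The open slot leaves the choice to discretion.

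The numerical objections largely stand:

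- Without prognostic value there is no inflation, and adjustment costs a little power.
- The calculation covers one cross-section and a linear outcome, whereas Aim 1 is framed as an odds ratio over two cohorts. If the effect is a group-by-cohort contrast, stable clinician factors largely cancel and the gain shrinks. If it is a pooled main effect over about 27 patients per clinician, the gain is larger (6–20% instead of 4–15% by the same formula). The article does not settle which applies.
- Joint allocation of clinicians who practise closely together makes balance less exact than the formula assumes.

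**Conclusion.** The point holds as a mismatch between design and analysis. The allocation balances sex and practice system in order to gain power; the only stated entry criterion will usually pass over them; and the remaining text merely permits clinician covariates. If the factors predict outcome and are left out, the reported standard errors are too large and the test is conservative. The harm is lost power, not bias or false positives.

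The size is conditional. At 13.8 patients per clinician and a linear outcome, inflation runs from nil, through about 4–15% (R² 0.2–0.4, ICC 0.05–0.10), to about 28% (R² 0.5, ICC 0.20). The ICC and R² are assumptions throughout. Under a logit model the figures would differ, and under a group-by-cohort contrast they would be smaller. That sex meets no entry threshold can be verified from Table 2; for practice system this is only an expectation.

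**What to change.** State in the Data management & analysis section that clinician sex and practice system enter every Aim 1 and Aim 2 model as fixed Level 2 covariates, whatever the observed baseline balance. The imbalance rule can remain for other variables.

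Both factors were used in the allocation, so no new data are needed, and the outcome analyses are described as still to come. The cost is about three between-clinician degrees of freedom (one for sex, two if practice system has three levels, which is assumed), leaving about 26 of 29. If the factors prove non-prognostic, this loses roughly 1–2 points of power.

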Next six months	----	27	
Six months to one year	----	22	
Not within the next year	----	23	
Importance of quitting, mean (SD)	----	7.9 (2.6)	
Confidence in quitting, mean (SD)	----	6.5 (2.9)	

The overall sample provides adequate power to conduct the planned analyses and detect moderate differences between intervention and delayed intervention groups. Power analyses prior to recruitment indicated a minimum sample of 28 physicians with 12 patients per cohort, with 10% loss to follow-up at each exit and six week survey. On average, 13.8 patients were enrolled for each of 31 clinicians participating in Cohorts 1 and 2 (range 8–17 patients). At baseline, study participants smoked a median of 10 cigarettes per day (IQR 5–20). Twenty-eight percent of participants reported considering quitting in the next month, 27% in the next six months, and 22% in the next year. Smoking was discussed in 64% of visits at baseline, and the average visit duration was 20.0 ± 9.2 minutes.

Exit surveys were completed an average of 1.7 days after the visit, with 24% completed more than 48 hours after the visit, and 2% completed after more than one week. On average, 6-week follow-up surveys were completed 42 days after the visit (range 36–71 days). Loss to follow up was minimal with only 6% (n = 50) of patients not completing the exit or 6 week survey. Less than 1% (n = 6) actively withdrew from the study after consent.

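### Closely linked clinicians from one practice were allocated jointly, but the mixed model has a random effect for clinician only, so the test of the TMCP effect is anti-conservative to an unreported, probably modest, degree

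*Protocol article*

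**What the plan says.** **Allocation.** The Randomization section of the protocol article states: "The unit of randomization for this study was the clinician". It then gives an exception. Where clinicians came from the same practice and "practiced closely together (e.g. shared patient panels, husband and wife practicing together) they were randomized together". The reason follows: "This decision was to reduce the chance of cross contamination through exposure to the intervention content by clinicians in the same practice". The number and size of such sets are not given.

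**Analysis.** Under Data management & analysis, outcomes are to be "adjusted for the clustering of patients within clinicians using generalized linear mixed models (GLMM"). The model is written out in two equations: patients at Level 1, clinicians at Level 2, the TMCP group indicator as a clinician-level predictor, and one random term, r0j. The text explains: "The clinician level (Level 2) models specify the relationship between the clinician-level predictors and the coefficients in the Level 1 model, with a random effect". There is no term for practice or for a jointly allocated set. For Aim 2: "The same generalized linear mixed model will be used with the indicator of TMCP group as the key independent variable".

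**Counting of units.** The Study design section says: "The study design is a group randomized trial of 31 clinicians". The power statement in Results also counts individuals: "Power analyses prior to recruitment indicated a minimum sample of 28 physicians with 12 patients per cohort, with 10% loss to follow-up".

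**The concern.** In a group randomized trial the variance of the treatment contrast depends on how many units were independently allocated and how alike members of a unit are. Two clinicians given one allocation always share an arm, so whatever their outcomes have in common adds to the difference between arms and does not average out as it would for two independent clinicians. A model whose top level is the clinician leaves that component out of the standard error.

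The section's own examples (shared panels, a married couple) and its reason for the rule (fear of contamination) make some positive correlation plausible. The stakes are a confidence interval that is too narrow and a false-positive rate above the nominal level, in a trial with only 31 clinicians and so little room to lose independent units.

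**Working it through.** **1. The plan's own figure.** The stated minimum of 28 physicians with 12 patients per cohort can be neither confirmed nor refuted, because alpha, power, ICC, control rate and a numerical effect size are not given. With two-sided alpha 0.05 and power 0.80 assumed, some plausible inputs return 28: odds ratio 2, control rate 0.4, ICC 0.01 and 10% loss (power 0.816), or a standardized difference of 0.4, ICC 0.05 and 10% loss (power 0.813). Others return anything from 12 to 102. The figure does not settle the point; it shows only that the count was made in physicians.

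**2. Inputs for the size of the problem.**
- Clinicians: 31 (Study design).
- Patients per clinician per cohort: m = 13.8 (Results).
- Assumed, because not stated: clinician ICC ρ = 0.05 to 0.10; share of clinician variance common to a pair φ = 0.5 to 0.8; sets are pairs; comparison in Cohort 2 alone.
- Fraction of clinicians in pairs, f: unknown, so varied.

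**3. Formulas.** The variance of a clinician mean is proportional to ρ + (1 − ρ)/m. Joint allocation adds f·φ·ρ. Hence

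variance inflation V = 1 + f·φ·ρ / [ρ + (1 − ρ)/m]

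ratio of true to reported standard error = √V

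actual type I error = 2·[1 − Φ(1.96/√V)]

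**4. The common factor.**
- ρ = 0.05: 0.05 / (0.05 + 0.95/13.8) = 0.05/0.1188 = 0.421.
- ρ = 0.10: 0.10 / (0.10 + 0.90/13.8) = 0.10/0.1652 = 0.605.

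**5. Results.** The low end uses ρ = 0.05, φ = 0.5; the high end uses ρ = 0.10, φ = 0.8.

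| Clinicians in pairs | f | V | True SE / reported SE | Type I error |
|---|---|---|---|---|
| none | 0 | 1 | 1 | 5.0% |
| 1 pair | 2/31 = 0.065 | 1.014–1.031 | 1.007–1.015 | 5.2–5.4% |
| 2 pairs | 4/31 = 0.129 | 1.027–1.062 | 1.013–1.031 | 5.3–5.7% |
| 20% (about 3 pairs) | 0.20 | 1.042–1.097 | 1.021–1.047 | 5.5–6.1% |
| 40% (about 6 pairs) | 0.40 | 1.084–1.194 | 1.041–1.093 | 6.0–7.3% |

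Worked example, high end at 40%: V = 1 + 0.4 × 0.8 × 0.605 = 1.194; √1.194 = 1.093; 1.96/1.093 = 1.794; two-sided tail 7.3%.

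**6. Degrees of freedom.** The normal reference in step 3 ignores the loss of units. A second calculation used m = 12, a t reference, and units minus 2 degrees of freedom, with wider assumptions (within-clinician ICC 0.05–0.20, between-colleague ICC 0.01–0.20). Two pairs leave 29 units (27 df, not 29) and a type I error of 5.2–6.1%; five pairs leave 26 units (24 df) and 5.5–7.9%. Simulating clinician means (20,000 replicates per scenario), with within-clinician ICC 0.10 and between-colleague ICC 0.05, gave 4.9% with no pairs, 5.2% with two and 6.4% with five. The direction is the same and the size similar.

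**The case against.** **The rule is narrow and disclosed.** It covers only same-practice clinicians who also worked closely together, and it is worded as a contingency. The text does not say how many sets arose, or show that any did. A reader might infer that all clinicians sharing a practice were allocated together. The documents do not support this: colleagues who did not work closely could be allocated separately. On that reading, with every clinician paired, the formula would give 7.5–10.8%; those figures should not be used.

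**The correlation is assumed.** No passage quantifies how alike linked colleagues' outcomes are, and shared panels is only an example. With 20% of clinician variance shared, ρ = 0.05 and two pairs, the type I error is 5.1%.

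**The calculation is not exactly the planned model.** The Aim 1 model contains a cohort indicator, so both cohorts enter. If the effect is estimated as a change from Cohort 1 to Cohort 2, the part of the shared variance that is stable over time cancels. Aim 1 also concerns behavior during smoking talk, which occurred in 64% of baseline visits: 0.64 × 13.8 = 8.8 visits per clinician, and two pairs then give 5.2–5.6%. Clinician-level covariates such as practice system may absorb some shared variance.

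**The degrees-of-freedom method is not stated.** A reader might infer that 29 degrees of freedom will be used; the article does not say so.

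**What stands.** These points limit the size. None makes jointly allocated clinicians independent. Nor is this simply detail left to a fuller plan: the article writes out the equations and the clustering level, and they do not match the allocation it describes.

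**Conclusion.** The mismatch holds on the text: for jointly allocated clinicians the randomized unit is the set, and the stated model for both aims has no level for it. The consequence is conditional. If sets exist and colleagues' outcomes are positively correlated, the standard error of the TMCP effect is too small and the test is anti-conservative.

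Under the step 2 assumptions the excess runs from negligible with a pair or two to a little over 2 percentage points with 40% of clinicians in pairs. The documents do not support calling the error large or the planned comparison invalid. Confidence is high in the mismatch and low in any particular figure. It is worth correcting because the outcome analyses were still ahead when the article was written and the change is small.

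**What to change.** 1. **Record a randomization-unit ID**: the set for jointly allocated clinicians, the clinician otherwise.
2. **Account for clustering at that level.** Add a random effect for the unit above clinician. With few sets this variance rests on little information and may be estimated at zero, or the model may not converge. Specify in advance that robust standard errors with a small-sample correction, clustered on the unit, will then be used.
3. **Take degrees of freedom** for the group effect from the number of randomized units.
4. **Correct the Randomization sentence** on the unit, and report the number of units and joint sets in each arm. That count alone shows how much the point matters.

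**Cost.** One extra ID variable, one model term with a stated fallback, and a corrected sentence. The confidence interval becomes slightly wider; with few sets the results should barely change.
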